### Data analysis

The primary data analysis will be performed on the basis of the intention-to-treat principle. We will compare baseline data for the two groups with Student’s *t* test, the chi-square test, or nonparametric tests. It is anticipated that a large proportion of values for the outcome variable will be missing, owing to dropout and nonresponse to the questionnaire. These data will be assumed missing at random, and therefore observed patient characteristics will be used to impute missing data by means of multiple imputation. Because it is expected that there will be a dropout rate of 13% (20 women) in each group and that some women will participate in the group training only a few times, in addition to the intention-to-treat analyses, we will perform a per-protocol analysis of the women who perform ≥75% of all training sessions.

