### Sample size estimation

The sample size estimation is based on the primary outcome—psychological well-being—measured by the WHO (Five) Well-being Index (WHO-5) [27]. A sample size calculation was carried out to detect a 10-point higher score on the WHO-5 at 29–34 weeks of gestation in the intervention group compared with the control group. A 10-point difference in the WHO-5 score between the intervention and control groups is considered clinically significant [28, 29], and an SD of 16 was used. This SD is based on a previous assessment of the WHO-5 score in a population of 3970 pregnant women with and without mental disorders measured at 10–12 weeks of gestation in the total population of pregnant women at Rigshospitalet, Copenhagen University Hospital. This SD value (16 points) was used in the sample size calculation because we did not have an SD in the WHO-5 score measured at 29–34 weeks at our disposal. We expect 50% of the participants to follow the program for at least 75% of the sessions (high participation, 19–24 sessions), whereas 35% will participate in 50% to 75% of the sessions (moderate participation, 12–18 sessions) and 15% will engage in less than half of the sessions (low participation). We expect high participation in the exercise intervention to lead to an increase of 10 points in the WHO-5 score, moderate participation to lead to an increase of 7 points, and low participation to lead to an increase of 2 points compared with the control group. This will lead to the intervention group’s having an average value 7.75 points (0.50 × 10 + 0.35 × 7 + 0.15 × 2) higher than that of the control group at 29–34 weeks of gestation. With a power of 90% and a two-sided significance level of 5%, a difference in well-being level of 7.75 points (SD 16) in the two groups at 29–34 weeks of gestation can be detected by a two-sample *t* test with 91 patients in each group.

We expect that it will be necessary to include a total of 300 pregnant women because we anticipate that 13% (20 women) in each group will drop out as a result of discomfort or complications related to pregnancy and that 39 women (30%) of the remaining 131 participants in each group will not answer the questionnaire at 29–34 weeks of gestation, leaving 91 participants in each group.

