### Intervention group

The intervention group will be offered an exercise program delivered to groups of 10–12 pregnant women at the hospital twice weekly for 12 weeks from baseline (17–22 weeks of gestation) in addition to standard antenatal care as described for the control group. The exercise program (*see* Table 1) will be carried out in accordance with the Danish national recommendations for exercise during pregnancy [30] and developed by physiotherapists from Rigshospitalet, Copenhagen University Hospital, who will also supervise the exercise sessions. The duration of a session will be 70 minutes, and one session will consist of a 10-minute warm-up (Borg scale 7–10); 20 minutes of endurance training on exercise bikes, treadmills, or cross-trainers (Borg scale 11–15); 25 minutes of strength training (back, abdomen, thighs, arms, and pelvic floor); and 15 minutes of stretching and relaxation (Borg scale 6) [31, 32].

**Table 1 Tab1:** Intervention group exercise program

Duration	Intervention	Description of exercise	Load
10 minutes	Warm-up Up to each teacher Has to include: • Light cardiovascular exercise • Mobilization of shoulder/back/pelvis	Examples: Neck stretching: standing in a circle, perform shoulder rotations and elevations Exercise of low intensity Walking in a circle: forward, backward, and sideways Shoulder/spine/pelvic mobility 1. Arm swings (one arm + both arms) 2. Arm swings in a kayak-paddling motion 3. Lateral flexions 4. Pelvic tilts (anterior, posterior, bilateral, figure eights) 5. On all fours, flexion/extension of the spine to find the neutral position	Borg Scale 7–10
20 minutes	Endurance training	Exercise bikes, treadmills, or cross-trainers	Borg Scale 11–15

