## Discussion

Antenatal depression and anxiety are associated with adverse complications such as preterm birth, which is a leading cause of infant morbidity [6], and result in emotional suffering for many pregnant women. The antenatal period theoretically offers an opportunity to implement preventive and effective interventions for pregnant women with mental illness and thereby reduce adverse outcomes and promote health for women and children. The EWE Study is therefore a highly relevant study and is, to our knowledge, the largest RCT designed to evaluate the effectiveness of supervised exercise in groups for improving psychological well-being among pregnant women at risk of depression. In addition to the large sample size, postnatal follow-up data will be provided, intention-to-treat analysis will be carried out, and the statistician performing the statistical analyses will be blinded to the allocation to the intervention or control group. Furthermore, baseline data will be collected to allow a comparison of the two groups, attendance at exercise classes will be documented, and data on safety and adverse events in the intervention group will be reported. These elements have been pointed out by authors of a meta-analysis as missing in previous RCTs on the topic [20]. The strongest risk factor for depression and anxiety during pregnancy or after delivery is a history of depression or anxiety prior to pregnancy [16]. It is therefore relevant to look at both diagnoses to improve psychological well-being among pregnant women at risk of depression. One study showed that depressive disorders and anxiety can be accompanied by a tendency for passivity and withdrawal, which may affect compliance [46]. However, a Danish study showed that the pregnant population attending Rigshospitalet, Copenhagen University Hospital, has a high proportion of well-educated women [47], who are associated with a high engagement in exercise [47]; therefore, we expect that compliance is in line with our expectations regarding this study population. This was also supported by the experiences in the pilot study. If proven effective, the intervention will offer a way for pregnant women at risk of depression or anxiety to actively do something to increase their physical and psychological well-being. The intervention is expected to be acceptable, feasible, cost-effective, and applicable, as well as being complementary to the existing antenatal care provided for this group of women.

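### The supplementary per-protocol analysis selects on attendance in the exercise arm only, so any comparison with controls is not randomized; its 75% cut also conflicts with the session counts at exactly 18 sessions

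*Protocol article*

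**What the plan says.** The Data analysis section of the protocol article makes intention to treat primary. Because dropout and low attendance are expected, it adds: "we will perform a per-protocol analysis of the women who perform ≥75% of all training sessions". It names no comparator for this set and gives no session count.

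The Intervention group section schedules sessions "twice weekly for 12 weeks from baseline (17–22 weeks of gestation". The Sample size estimation section divides the exercise arm into three bands:

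- High: "We expect 50% of the participants to follow the program for at least 75% of the sessions (high participation, 19–24 sessions"), with an assumed gain of 10 points on the WHO-5.
- Moderate: "35% will participate in 50% to 75% of the sessions (moderate participation, 12–18 sessions"), with an assumed gain of 7 points.
- Low: "15% will engage in less than half of the sessions (low participation"), with an assumed gain of 2 points.

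The Discussion reports one study in which "depressive disorders and anxiety can be accompanied by a tendency for passivity and withdrawal, which may affect compliance". It then argues that the hospital's well-educated population, and the pilot experience, make the expected compliance realistic. It also says that class attendance will be documented.

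**The concern.** Attendance is observed after randomization and in one arm only. The women who reach 75% are a self-selected part of the exercise arm, and no matching part of the control arm can be identified. If the traits that keep a woman coming also predict her well-being at 29–34 weeks, the comparison mixes the effect of exercise with a prior difference between women. The outcome is well-being, and the Discussion itself links depression and anxiety to withdrawal, so such a relation is plausible here. A reader could then take a supplementary estimate for the effect of completing the programme when part of it is selection.

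The membership rule is also stated in two ways that disagree at one value, so the set is not uniquely defined.

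**Working it through.** **The plan's own figures.** Average effect: 0.50 × 10 + 0.35 × 7 + 0.15 × 2 = 7.75 points. With SD 16, two-sided 5% and 90% power, a two-sample t test needs 90.54, rounded up to 91 per group; power at 91 is 90.1%. Both stated figures reproduce.

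**Session count.** 2 × 12 = 24 sessions.

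| Sessions | Share of 24 | ≥75%? (Data analysis) | Band by count (Sample size estimation) |
|---|---|---|---|
| 17 | 70.8% | no | moderate |
| 18 | 75.0% | yes | moderate |
| 19 | 79.2% | yes | high |

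The two rules part at 18 only. The Sample size estimation section also disagrees with itself there, since "at least 75% of the sessions (high participation, 19–24 sessions") leaves out 18 and "moderate participation, 12–18 sessions" takes it in. The 7.75 uses the assumed shares (50/35/15%), not the session counts, so neither it nor the 91 depends on where 18 falls.

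**Size of the per-protocol set.** At 50%: 0.5 × 150 = 75 randomized women, or 0.5 × 91 = 45.5 of those analysable, if the 50% also holds among responders (an assumption).

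**Selection bias.** Let p = 0.5 be the share reaching 75%, and g the difference in untreated WHO-5 at 29–34 weeks between these women and the rest of the arm. By randomization, the controls' expected mean equals the untreated mean of the whole exercise arm. Attenders differ from that by (1 − p)·g = 0.5·g. The document gives no g, so the values below are assumptions.

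| Assumed g | Bias = 0.5·g | Share of 7.75 | Chance that a 5% test rejects with no effect |
|---|---|---|---|
| 0 | 0 | 0% | 5% |
| 4 | 2 | 26% | 11% |
| 6 | 3 | 39% | 18% |
| 8 | 4 | 52% | 28% |

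The last column is for an unadjusted comparison of 46 attenders with 91 controls: SE = 16 × √(1/46 + 1/91) = 2.89, with a normal approximation. A simulation of 20,000 null trials gave 10%, 18% and 29% for g = 4, 6 and 8. A negative g reverses the sign of the bias.

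The same range as a correlation: if attendance and untreated WHO-5 are bivariate normal with correlation ρ and the upper half attend, the bias is ρ × 16 × 0.399/0.5 = 12.77·ρ. This is 1.3, 2.6 and 3.8 points at ρ = 0.1, 0.2 and 0.3. A bias of 2–4 points thus corresponds to ρ of about 0.16–0.31.

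**Which exposure for an instrumental-variable estimate.** With attendance as yes/no at 75%, the plan's own assumptions give 7.75/0.5 = 15.5, not the 10 points assumed for high attenders, because women below the cut are assumed to gain 7 or 2 points. With the number of sessions at the midpoints of the printed bands (21.5, 15 and, for 0–11, 5.5), mean attendance is 0.5 × 21.5 + 0.35 × 15 + 0.15 × 5.5 = 16.825. The slope is 7.75/16.825 = 0.461 points per session, or 0.461 × 21.5 = 9.9 at the high-band midpoint, close to 10. Linearity is approximate: the assumed gains per session are 10/21.5 = 0.465, 7/15 = 0.467 and 2/5.5 = 0.364.

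**The case against.** The strongest reply is that the analysis is only supplementary. Intention to treat is primary, the Discussion presents it as a strength of the trial, and nothing says that the per-protocol result will carry the conclusion. That stands, and it limits the weight of the point.

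A reader might also infer that the protocol admits depression lowers compliance and that the estimate is therefore biased upward. The document does not support this. It says only that passivity and withdrawal may affect compliance, and goes on to argue that compliance will be as planned. It does not say that, within a sample recruited entirely for risk, attenders would have higher untreated WHO-5 scores. That reassurance, however, concerns the average level of compliance, not whether attenders resemble non-attenders.

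The comparator is inferred: Data analysis names none, and adjustment for baseline WHO-5 may be in a statistical analysis plan that is not shown. Adjustment could reduce the bias but would not restore randomization.

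On the session count, the ≥75% rule in Data analysis is clear in itself; the conflicting counts are in the sample size reasoning and affect only women with exactly 18 sessions.

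Finally, an instrumental-variable analysis has its own assumptions. Encouragement from general practitioners and the weekly supportive emails could act on well-being outside the sessions. This stands and belongs in the plan.

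**Conclusion.** The point holds in a limited form. As written, the plan provides a supplementary analysis of roughly half the exercise arm, selected after randomization by a criterion that cannot be applied to controls, so a comparison with controls is not a randomized one. Upward bias is the more likely direction if less depressed women attend more, but that is a judgement. The 2–4 points and the 11–28% rejection rates rest on an assumed g of 4–8 and an unadjusted comparison; at g = 0 there is no bias.

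The conflict at 18 sessions is certain but small. The primary analysis, the 7.75 points and the 91 per group are unaffected. The analysis wording should be changed before unblinding, but the trial's main conclusion does not depend on it.

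**What to change.** 1. Keep intention to treat as the primary analysis.
2. Estimate the effect of attendance by a two-stage instrumental-variable analysis: allocation as instrument, documented number of sessions (0–24) as exposure, adjusted for baseline WHO-5. Use the session count rather than a yes/no at 75%.
3. State its assumptions: allocation affects well-being only through sessions (which the emails and practitioner encouragement could violate), and the effect is roughly linear in sessions.
4. If the ≥75% set is kept, label it descriptive and non-randomized, and state its comparator.
5. Reconcile Data analysis and Sample size estimation at 18 sessions, so that one rule, given as both a percentage and a count, appears in both.

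The cost is analysis wording only, since attendance is already to be recorded. The price is a wider interval than the per-protocol comparison would show, and reliance on the assumptions in item 3.

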### Pilot study

Before initiating a full-scale trial, a pilot study with 20 participants was conducted from April to June 2016. This was done to examine the recruitment procedure, dropout rates, and acceptability of and compliance with the exercise program and the questionnaires [45]. The experiences of the participants and key health care professionals involved in the project were registered and evaluated. The proportion of pregnant women eligible for participation in the study and who wished to participate were as expected, and we therefore expect to be able to recruit the needed 300 participants according to the study power calculation. Compliance among the nine pregnant women in the intervention group participating in the pilot study was acceptable. The pilot study led to minor changes. Hand grip strength measurement (by North Coast Hydraulic Hand Dynamometer) was included at baseline to provide an objective measure of total muscle strength [26]. The STAI was added to the questionnaires because a large proportion of the participants had anxiety prior to pregnancy; use of a specific measure of anxiety is therefore relevant. Furthermore, the PSQI was added to the questionnaires because participants reported that their quality of sleep had improved during the intervention period. Finally, at the request of the participants, the exercise intervention was adjusted so that it is possible to choose between treadmills and cross-trainers in addition to exercise bikes during the endurance training part of the intervention, instead of exercise bikes being the only option.

## Discussion

Antenatal depression and anxiety are associated with adverse complications such as preterm birth, which is a leading cause of infant morbidity [6], and result in emotional suffering for many pregnant women. The antenatal period theoretically offers an opportunity to implement preventive and effective interventions for pregnant women with mental illness and thereby reduce adverse outcomes and promote health for women and children. The EWE Study is therefore a highly relevant study and is, to our knowledge, the largest RCT designed to evaluate the effectiveness of supervised exercise in groups for improving psychological well-being among pregnant women at risk of depression. In addition to the large sample size, postnatal follow-up data will be provided, intention-to-treat analysis will be carried out, and the statistician performing the statistical analyses will be blinded to the allocation to the intervention or control group. Furthermore, baseline data will be collected to allow a comparison of the two groups, attendance at exercise classes will be documented, and data on safety and adverse events in the intervention group will be reported. These elements have been pointed out by authors of a meta-analysis as missing in previous RCTs on the topic [20]. The strongest risk factor for depression and anxiety during pregnancy or after delivery is a history of depression or anxiety prior to pregnancy [16]. It is therefore relevant to look at both diagnoses to improve psychological well-being among pregnant women at risk of depression. One study showed that depressive disorders and anxiety can be accompanied by a tendency for passivity and withdrawal, which may affect compliance [46]. However, a Danish study showed that the pregnant population attending Rigshospitalet, Copenhagen University Hospital, has a high proportion of well-educated women [47], who are associated with a high engagement in exercise [47]; therefore, we expect that compliance is in line with our expectations regarding this study population. This was also supported by the experiences in the pilot study. If proven effective, the intervention will offer a way for pregnant women at risk of depression or anxiety to actively do something to increase their physical and psychological well-being. The intervention is expected to be acceptable, feasible, cost-effective, and applicable, as well as being complementary to the existing antenatal care provided for this group of women.

To conclude, we have described a protocol for an RCT aimed at evaluating whether supervised exercise in groups for pregnant women with a current or previous history of depression and/or anxiety improves psychological well-being during pregnancy. The results will provide evidence useful for the organization of care for pregnant women and their families.

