## Abstract

**Background:**

Pregnant women with depression and/or anxiety prior to pregnancy are at higher risk of preterm birth, breastfeeding problems, postpartum depression, and disruption of the mother-infant attachment. It is well documented that exercise improves psychological well-being in nonpregnant subjects with symptoms of depression. However, in only a few small studies have researchers examined the effect of exercise on symptoms of depression among pregnant women. We hypothesize that physiotherapist-supervised group exercise for pregnant women at risk of antenatal depression increases their psychological well-being. This paper describes the study protocol of a randomized controlled trial (RCT) on a supervised group exercise intervention for pregnant women with a current or previous history of depression and/or anxiety.

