**Methods/design:**

The RCT is being carried out at the Department of Obstetrics, Rigshospitalet, Copenhagen University Hospital, in the period 2016–2019. The inclusion criteria are pregnant women ≥18 years of age with depression and/or anxiety requiring treatment by a psychiatrist or a psychologist within the last 10 years and/or intake of antidepressants in the 3 months prior to conception and/or during pregnancy. The women must have appropriate Danish language skills, be pregnant with a single fetus, give written informed consent, and be at 17–22 gestational weeks when the intervention begins. The primary outcome is psychological well-being (the five-item World Health Organization Well-being Index). Secondary outcomes are symptoms of depression (Edinburgh Postnatal Depression Scale), functional ability (General Health Questionnaire), clinical symptoms of anxiety (State-Trait Anxiety Inventory), sleep quality and sleep disturbances (Pittsburgh Sleep Quality Index), and pregnancy and delivery outcomes. The intervention is supervised group exercise twice weekly for 12 weeks. The control group will receive standard antenatal care. On the basis of sample size calculation, a total of 300 women will be randomly assigned to either the intervention or the control group in a ratio of 1:1.

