*Sleep quality and sleep disturbances*, measured by the Pittsburgh Sleep Quality Index (PSQI). The PSQI is a subjective scale measuring sleep quality and sleep disturbances over a 1-month period [43]. The scale addresses quantitative aspects of sleep, such as sleep latency and sleep duration, as well as more subjective aspects, such as restfulness of sleep [43]. Overall sleep quality is measured by means of 19 questions, and the total score is based on 7 “component” scores, each of which has a range of 0–3 points. A score of 0 indicates no difficulty, whereas a score of 3 indicates severe difficulty. The sum of the component scores results in a “global” score ranging from 0 to 21 points, where 21 indicates severe sleep problems. The PSQI has been found to be useful in pregnancy research, and good internal consistency and construct validity have been reported [44].
*Pregnancy and delivery outcomes*, comprising sick leave (measured in days), hospitalization (measured in number of hospital admissions and days), labor onset (spontaneous or induced), use of epidural anesthesia during delivery (yes or no), duration of labor (measured in hours), mode of delivery (percentage of participants with spontaneous delivery, vacuum extraction, or cesarean section), birthweight (measured in kilograms), and birth length (measured in centimeters). This information will be obtained from patient records.

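### Adverse events are planned for the intervention group alone and preterm birth is not an outcome, so the between-arm safety comparison is incomplete

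*Protocol article*

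**What the plan says.** Adverse events are mentioned once in the protocol article, in the Discussion, among features said to have been missing from earlier trials: "data on safety and adverse events in the intervention group will be reported".

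Under Secondary outcomes, the fifth item is a closed list of pregnancy and delivery outcomes, "comprising sick leave (measured in days), hospitalization (measured in number of hospital admissions and days), labor onset (spontaneous or induced", followed by epidural use, labor duration, mode of delivery, and "birthweight (measured in kilograms), and birth length (measured in centimeters". The source is given without restriction to one arm: "This information will be obtained from patient records". Neither gestational age at birth nor preterm birth is in the list.

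Preterm birth is nonetheless central to the rationale. The abstract describes the target population as "at higher risk of preterm birth, breastfeeding problems, postpartum depression", and the Discussion opens with "Antenatal depression and anxiety are associated with adverse complications such as preterm birth, which is a leading cause of infant morbidity".

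Two further places matter. The Withdrawal section names four complications (pelvic instability, preeclampsia, vaginal bleeding, preterm labor symptoms) and applies them to participants in general. The Sample size estimation section expects 13%, or 20 women, to be lost in each group through discomfort or pregnancy complications.

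**The concern.** The complications of interest occur in pregnancy with or without exercise. A count in the exercise arm alone cannot show whether exercise raised, lowered or left unchanged their frequency; that needs the rate in the randomized controls. The plan has those controls and already goes to patient records for other outcomes, but its one sentence on adverse events names only the intervention group.

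The gap in the delivery outcomes compounds this. A lower mean birthweight in one arm could reflect earlier delivery, slower growth or both. Without gestational age, a listed secondary outcome is hard to interpret, and the complication that the article puts at the front of its rationale is not compared at all.

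At stake is what the trial can report about the safety of a program that the Discussion puts forward as a complement to existing antenatal care. A one-arm count could be read as reassurance or as a warning, with no basis for either.

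**Working it through.** **Step 1: which outcomes have a planned comparison between arms.** This part rests on the text.

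| Outcome | Where named | Comparison between arms planned? |
|---|---|---|
| Hospital admissions and days, sick leave | Secondary outcomes | Yes |
| Labor onset, epidural, labor duration, mode of delivery | Secondary outcomes | Yes |
| Birthweight, birth length | Secondary outcomes | Yes, but without gestational age |
| Preeclampsia, vaginal bleeding, preterm labor symptoms, pelvic instability | Withdrawal | No |
| Preterm birth, gestational age at birth | Preterm birth in the rationale only | No |
| Adverse events generally | Discussion | No; intervention group named alone |

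The plan itself expects the fourth row to occur in both arms: the withdrawal criteria are not tied to an arm, and complication-related loss is set at 13% in each.

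**Step 2: the number of women available.** The plan gives no figure for safety, so the only stated number to reproduce is the sample size. For a difference of 7.75 points, SD 16, two-sided 5% and 90% power, the two-sample t test needs 90.5, so 91 per group, as stated. Allowing for both losses, 91 / (0.87 × 0.70) = 149.4, so 150 per group and 300 in total, also as stated. Outcomes taken from records do not depend on questionnaire response, so up to 150 per arm could contribute.

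**Step 3: precision of a comparison by assigned group.** The documents give no rate for preterm birth or any other complication, so control rates p of 5%, 8%, 10% and 15% are assumed. With n = 150 per arm and equal rates, the 95% half-width for the risk difference is 1.96 × √(2p(1 − p)/n). At p = 0.10 this is 1.96 × √(2 × 0.10 × 0.90/150) = 1.96 × 0.0346 = 0.068.

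Power against p₂ uses the normal approximation, with p̄ the mean of the two rates: Φ{[|p₂ − p| − 1.96√(2p̄(1 − p̄)/n)] / √([p(1 − p) + p₂(1 − p₂)]/n)}. For 8% against 16%: (0.080 − 1.96 × 0.0375) / 0.0372 ≈ 0.17, giving power of 57%.

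| Assumed control rate | 95% half-width (percentage points) | Power, doubling | Power, halving |
|---|---|---|---|
| 5% | 4.9 | 38% | 21% |
| 8% | 6.1 | 57% | 31% |
| 10% | 6.8 | 68% | 38% |
| 15% | 8.1 | 88% | 54% |

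A comparison would give an unconfounded estimate with an honest interval. Only a doubling from the highest assumed rate would be detected with more than 80% power.

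**The case against.** The strongest reply is that the trial does compare pregnancy outcomes between arms. A reader might infer from the adverse event sentence that the trial cannot say anything about whether exercise affects pregnancy complications. The documents do not support that: admissions, labor onset, mode of delivery and birthweight are secondary outcomes from records, not limited to one arm, and a complication serious enough for admission would count there. This stands, and it is why the point is incompleteness. It does not close the gap, because the list covers the number and length of admissions, not their reasons, and milder events would not appear.

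Second, the sentence is one clause in a list of strengths, not an adverse event section. It may be aimed at events during exercise sessions, which have no control counterpart, and it does not say that control events will go uncollected. The full protocol, the SPIRIT checklist and the figures are not shown and may say more. That is a fair caution against inferring that control data will not exist. Still, the scope is stated in words, not merely left unsaid, and should be corrected or clarified.

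Third, the objective is psychological well-being, and nothing claims that the trial tests an effect on preterm birth. Step 3 shows that the estimate would be imprecise. Both are true. They argue against a powered test, not against reporting gestational age, which birthweight needs in any case.

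Finally, the 13% loss might be read as an adverse event rate for the exercise arm. It is an expected dropout figure, stated for each group, and is not used that way here.

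**Conclusion.** The point holds in limited form. As written, the plan yields one-arm adverse event data for complications that it expects in both arms, and its enumerated delivery outcomes omit gestational age at birth and preterm birth. Several pregnancy and delivery outcomes remain properly comparable; the named complications and preterm birth do not have a planned comparison, and birthweight is ambiguous without gestational age.

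Repairing this would give risk differences with 95% half-widths of about 5 to 8 percentage points. That range rests on assumed rates of 5% to 15%, equal in the two arms, and on records being available for all 150 women per arm. The article does not say whether record follow-up continues after withdrawal. If it stopped, women with the very complications of interest would be lost from the comparison.

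**What to change.** Reword the Discussion sentence, and the corresponding part of the full protocol if it reads the same way, so that the complications already named under Withdrawal are extracted from patient records for all randomized women, including those withdrawn, and reported by assigned group as risk differences with 95% confidence intervals. Keep injuries and other events during exercise sessions as a separate list for the intervention arm, labeled as having no comparator.

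Add gestational age at birth and preterm birth, with its gestational-age cutoff stated, to the pregnancy and delivery outcomes. State that birthweight will be interpreted together with gestational age.

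The cost is a few more fields in an extraction already planned, with no extra visits and no change to care. Recruitment was still under way at publication, so this could be fixed before analysis. The price in interpretation is wide intervals for uncommon events; the text should say that these are estimates and that absence of a significant difference is not evidence of safety.
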